### Study Sample and Inclusion Criteria

This study is a two-armed randomized controlled trial that was conducted with a sample of women of reproductive age from urban Lilongwe, Malawi. The study consists of a baseline survey, followed by the randomization of women into intervention and control arms and the implementation of the 2-year family planning intervention. Two follow-up surveys were conducted 1 and 2 years after the baseline survey. Figure 1 outlines the general framework of the complete field experiment.

**Figure 1 figure1:**
[figure not shown]
Experimental framework and flowchart.

For the study, we recruited women who, at the time of the baseline survey, (1) were married, (2) were either currently pregnant or had given birth within 6 months from the time of the baseline screening, (3) were between the ages of 18 and 35 years, and (4) lived in the city of Lilongwe. Women who successfully met these criteria and consented to participate in the study were recruited. In addition, no 2 eligible women were enrolled from the same household. If multiple women from the same household were potentially eligible to be recruited based on the 4 inclusion criteria above, the youngest eligible woman from the household was chosen to participate—given that randomization was to be administered at the individual woman level, it was necessary for us to select only 1 eligible woman from a household to minimize any possible contamination across women in the intervention and control groups. We also ensured that eligible women who were selected for the study were sufficiently distant (at least five households apart) from each other, which also served to reduce any spillover effects between treated and control women who lived in the same neighborhood. Following the recruitment of women, 1 member from the recruited woman’s household was identified and selected to respond to sections in the baseline and follow-up surveys that inquired about household expenditures, assets, and consumption. The household member selected for this part of the study was required to meet the following inclusion criteria: (1) he or she was >18 years old, (2) he or she was a resident of the same household from which the woman respondent described above was selected, and (3) he or she claimed to be knowledgeable about the household’s financial status, consumption, and expenditure. The household member who successfully met these inclusion criteria and who consented to participate in this part of the study was recruited to participate. Finally, children in the household were recruited to complete an anthropometric module, including data collection of height, weight, and anemia status at baseline and again at the 2 follow-ups. The children who were selected from the household for this part of the study (1) were aged <6 years, (2) were identified as the biological or adopted children of the woman who was recruited for the main part of the study, and (3) resided in the same household as the eligible woman. Children who successfully met these inclusion criteria and whose mothers consented to them participating in this part of the study were recruited to participate.

### Recruitment and Study Timeline

Using the most recent Demographic and Health Survey (DHS) and census maps of Lilongwe’s enumeration areas and listings of households and neighborhoods, which were provided to us by the Malawi MOH; National Statistics Office (NSO); and our implementation partner, Innovations for Poverty Action (IPA) Malawi, we employed a two-stage sample selection procedure that was based on the sampling strategy used by the DHS. In the first stage, we randomly selected areas in Lilongwe to be surveyed until we selected enough areas to contain at least 11,000 households in total. In the second stage, our surveyors proceeded door-to-door to screen households in each selected area for potentially eligible women. Surveyors continued to screen households until they identified at least 2000 women for the study in accordance with the inclusion criteria listed above, and these eligible women were recruited in accordance with the recruitment protocols outlined below. Surveyors used a recruitment script to verify eligibility and presented the eligible woman with a consent form to participate in the study. Written informed consent was obtained from all participating women before proceeding to administer the baseline survey. Multimedia Appendix 1 shows recruitment script and the consent form that were administered to the women respondents. Women who met the eligibility criteria and who consented to participate in the study were recruited into the study. On the basis of our knowledge of participation refusal rates and the estimated number of eligible women in Lilongwe, we estimated the need to screen an estimated 3000 households to obtain a desired sample size of at least 2000 women. We required a study sample of at least 2000 women to achieve sufficient power to measure our outcomes of interest; see our power calculations below. As women who were selected into the study would also be at least five households apart from each other, we would need to choose enough enumeration areas to have at least 11,000 households in total (2000×5=10,000 households among the women who make up our sample and who are at least five households apart, plus an additional 1000 households that were screened but where women either did not meet the eligibility criteria or refused to participate). Recruitment from the selected enumeration areas ceased once at least 2000 women were found who met the eligibility criteria, consented to participate in the study, and were administered the baseline survey.

The planned experiment spanned 42 months. Table 1 shows the study timeline. Before recruiting and conducting the study with the main study sample, a small sample of women was recruited as a means to pilot new survey instruments and intervention activities over the study period. All research activities, including recruitment, consent, study instrument administration, and intervention administration, were administered to the pilot sample using the same study protocols as those used for the main sample. For this reason, the final analytic data sets for the study consist of data from both the pilot and main samples.

**Table 1 table1:** Study timeline.

Study activities	Months													
	1-3	4-6	7-9	10-12	13-15	16-18	19-21	22-24	25-27	28-30	31-33	34-36	37-39	40-42
Prepare survey instrument; hire study staff and interventionists; obtain IRB^a^, partner, and local approvals; identify and finalize sampling strategy	✓	✓	✓	—^b^	—	—	—	—	—	—	—	—	—	—
Training of local staff, lay interventionists, and enumerators	—	—	—	✓	—	—	—	—	—	—	—	—	—	—
Household screening and sample recruitment	—	—	—	✓	✓	—	—	—	—	—	—	—	—	—
Baseline survey administration, randomization, and intervention administration	—	—	—	—	✓	—	—	—	—	—	—	—	—	—
Intervention period	—	—	—	—	✓	✓	✓	✓	✓	✓	✓	✓	—	—
First-year follow-up and analysis	—	—	—	—	—	—	—	—	✓	—	—	—	—	—
Intervention study close-out, second-year follow-up, and analysis	—	—	—	—	—	—	—	—	—	—	—	—	✓	—
Final reports, publications, and dissemination	—	—	—	—	—	—	—	—	—	—	—	—	✓	✓

^a^IRB: Institutional Review Board.

^b^—: indicates the month in which that specific study activity is not taking place (eg, the preparation of the survey instruments only take place in the first 9 months and is completed by then).

### Informed Consent and Participant Privacy

The process to obtain consent was consistent for all potential participants: women, financially knowledgeable members of the household, and children <6 years. Written consent to participate was obtained from all participants before administering each survey (baseline and annual follow-ups). Once participants agreed to join the study, a copy of the consent form script was read to them and they were given opportunities to ask questions and express concerns. Surveyors checked for comprehension throughout the consent process. This process was estimated to take between 5 and 10 min, although it took longer if a participant had many questions—refer to the consent documents in Multimedia Appendix 1 for details concerning the consent process. After completing the consent script, potential participants were encouraged to ask questions and asked if they would like to participate. If the participant wished to take further time to reflect, the surveyor and the participant determined the time and method of reconnecting. If the potential participant agreed to be a part of the study, consent was obtained and documented by obtaining the signatures of both the participant and the study staff member who conducted the consent discussion. Upon consenting, the surveyor then conducted the survey.

For follow-up surveys, verbal consent to participate was obtained over the phone from only those participants who were originally recruited at baseline but since either moved outside of Lilongwe or were unreachable in person after 3 contact attempts. The only respondents who were recontacted for the phone follow-up survey were those respondents who were simply lost to follow-up. Respondents who had previously indicated that they were no longer interested in participating in the study were not contacted.

Throughout the consent process, the surveyor clearly explained to the participant that even if she decided to participate and sign the consent form, she could decide at any time to end her participation. If the study participant was not literate, then a witness who did not work for the study signed the consent form. In the absence of witnesses, the participant could confirm their consent by placing a thumbprint on their consent form and a photo of the thumbprint was taken as a record of consent. Moreover, participants were encouraged to contact the researchers with any further questions during the informed consent discussion or any time during the study. Consent was obtained before any surveys were conducted. All participants were informed that their participation was completely voluntary and that they could choose not to participate in the study or to end their participation in the study at any time.

The recruitment scripts, consent forms, and survey instruments were translated from English into Chichewa by a certified translator.

With regard to consent during the administration of the intervention, women were informed that they could take part in any component of the interventions that was offered to them; they could take up and stop any or all components of the intervention at any time. For example, counselors asked for a woman’s consent to participate in a counseling session each time they visited a woman’s home.

All surveys and administration of the intervention were conducted in a private room. To maintain a respondent’s privacy during an attempt to reach her by phone, the field enumerator conducting the call left no indication of the reason for the phone attempt (eg, voicemail, text message) on the respondent’s phone should there be no response to a call. Any disruption or interruption during the interview, either in person or by phone, resulted in the postponement or termination of the interview.

### Randomization

Following the baseline survey, women who consented to participate in the study were individually randomized into 1 of 2 experimental arms: an intervention arm or a control arm. The women were randomized to the intervention and control groups such that intervention assignment was balanced according to the following baseline characteristics: neighborhood or household cluster, distance to the nearest family planning clinic, number of living children, months since last live birth, current use of family planning, age of marriage, educational attainment, and household wealth. As part of the balancing process, strata by each combination of characteristic values were created and observations were assigned to their respective strata. Observations within each stratum were then individually randomized by the Principal Investigators in a 1:1 allocation to either the treatment or the control group using computer-generated randomization through STATA, version 13 (StataCorp). Block randomization was not used in this study. Following individual randomization, the IPA Malawi intervention team implemented the intervention to the participants who were randomized into the intervention arm.

### The Intervention

Following randomization of women into the intervention and control arms, women assigned to the intervention arm were offered the following 3 intervention components over a 2-year period:

Transportation component: women were offered a free transportation service from their homes to our partner family planning clinic, the Good Health Kauma Clinic. The transportation service was provided by a driver who was hired and trained by our local implementation partner, IPA Malawi. Women received the driver’s phone number and were instructed to contact the driver to transport them to the Good Health Kauma Clinic during the clinic’s normal working hours, which are between 8 AM and 5 PM from Monday to Saturday. The driver maintained a daily schedule of the women who requested his services, and women were instructed to notify the driver at least one day before they wished to go to the clinic to make sure that the driver was able to transport them. The driver also provided 1 day’s notice to the Good Health Kauma Clinic to inform them of how many women from the study could be expected to attend the clinic on the following day. The Good Health Kauma Clinic assured the project team that women in the intervention arm who come for services would not have to wait more than 1 hour before being examined by a medical professional. In addition, one of our female field managers from IPA Malawi accompanied the driver at all times. Although all women in the intervention arm were presented with pictures of the field team (and could therefore recognize our team members), the presence of another woman in the vehicle served to minimize potential stigma associated with a woman traveling alone in the company of another man.Counseling component: women who were assigned to the intervention arm were also offered free, private family planning counseling sessions over the 2-year intervention period. The counseling sessions were provided by trained counselors and included a risk assessment for clinical methods and detailed information on methods switching; side effects associated with each method; and the benefits of contraception, birth spacing, and dual protection. Consultations were designed to promote informed choice by discussing common misperceptions surrounding family planning and the use of modern contraceptives. Women received a detailed information brochure on birth spacing and side effects and also received counseling on both modern and natural family planning methods, in 
Multimedia Appendix 2.
Strategies on how to communicate family planning messages with partners and on how to increase partner awareness were conveyed during sessions. Counseling sessions were scheduled to last no more than 1 hour per session and were administered in a private room by a counselor who was trained to provide family planning and reproductive health services. Counselors were hired and trained by IPA Malawi. We enlisted the support of the Malawi Reproductive Health Directorate (RHD) and several international nongovernmental organizations who work on family planning, including Population Services International (PSI), Banja La Mtsogolo (BLM), the Family Planning Association of Malawi (FPAM), and FHI360, to help us develop training materials, brochures and flyers, and other counseling resources. We also collaborated with the Malawi RHD, BLM, and PSI to assist with the counselor training. Women in the intervention arm received a total of 6 counseling sessions, 1 comprehensive 90-min session just after administration of the baseline (within 1 month) and 5 shorter 45-min follow-up sessions that were spaced out over the 2-year intervention period. The first session introduced women to the range of available family planning methods and counseled women on side effects. In the first session, counselors also informed women in the intervention arm about the transport service (described above) and side effects management service (described below) that were available to them and provided women with the necessary information on how to access these services. Counselors also provided their phone numbers to women and were on call over the course of the study period to respond to any questions and concerns.Financial reimbursement component: women who were assigned to the intervention arm were financially reimbursed for any out-of-pocket expenditures that they incurred for receiving family planning care at the Good Health Kauma Clinic. Costs that were reimbursed at the Good Health Kauma Clinic included costs related to the procurement of family planning medications and contraceptive methods, family planning consultation fees, lab test fees, and exam fees. The reimbursement allowance for each woman was 17,500 MKW (US $25.00) and could be redeemed by the woman over multiple visits at the Good Health Kauma Clinic over the 2-year intervention period. For every family planning service that the woman received, the cost of the service was deducted from her reimbursement allowance of 17,500 MKW.

In addition, women who were assigned to the intervention arm and who experienced any side effects because of contraceptive use over the course of the 2-year intervention period received a series of services for the treatment of side effects. In the event that a woman in the intervention arm experienced a side effect or contraindication, she could contact a trained Obstetrician-Gynecologist at the Kamuzu College of Medicine in Lilongwe, via telephone, and would receive advice on how she can best seek care. The doctor would conduct a preliminary telephone consultation and would refer the woman over the phone to seek care at their nearest public clinic, public hospital, or the Good Health Kauma Clinic. All women in the intervention arm also received an *emergency package* during the first counseling visit from the counselor (see above). This *emergency package* consisted of (1) a transport voucher, equivalent to an estimated 6500 MWK (US $9.28) and (2) a mobile phone credit scratch card for the mobile provider of their choice, equivalent to 500 MWK (US $0.72). A template of the transport voucher is provided in Multimedia Appendix 3. This *emergency package* was given to all women in the intervention arm, regardless of whether they took up any intervention component or experienced a side effect. The counselor informed the woman that, in addition to the other side effects management services mentioned above, the woman could use the *emergency package* that she was given to cover (1) any phone airtime costs that she used to have a consultation with one of the doctors who are on call and (2) any emergency transport costs (taxi) she incurred to travel to a health facility where she can receive treatment for her contraceptive-related side effects. The transport voucher could be presented to any taxi driver in the city of Lilongwe and the taxi driver would, in turn, redeem the voucher at the IPA Malawi office in exchange for cash equivalent to the cost of the trip. The woman was asked to keep receipts of any costs she incurred at the health facility so that she could be reimbursed later. Costs for which the woman could be reimbursed included costs of medications and lab tests, costs of additional consultations at the health facility, and costs of switching or discontinuing methods. The maximum reimbursement amount that a woman was eligible to receive for the treatment of family planning-related side effects or contraindications is 35,000 MWK (US $50.00) over the 2-year intervention period. The reimbursement could be applied to cover the cost of treatment for side effects for all family planning methods used by the woman, regardless of where the method or treatment was procured. All reimbursements for incurred costs were distributed as closely as possible to the time that the reimbursable cost was incurred.

Following the randomization of women into the intervention and control arms, women who were assigned to the intervention arm were visited by the family planning counselor. During this initial visit, the counselor described all 3 intervention components, including their terms and conditions, to the woman. The counselor answered any questions that the woman may have had about the intervention and then asked for and confirmed the woman’s consent to participate in the intervention using a Terms of Service document (available upon request). Each woman received a paper copy of the Terms of Service document. If the woman consented to participate, the counselor then administered the first counseling session. Women assigned to the intervention arm could withdraw their participation from any intervention activity at any time and could also rejoin at any time without any penalty over the 2-year intervention period.

### Control Arm

Women who are assigned to the control arm received a package of publicly available literature and information on the benefits of family planning as well as information about their nearest family planning clinic. This information package was delivered to all women at the time of the baseline interview. Women in the control arm were only recontacted by the research team at follow-up.

### Participant Compensation

All women who participated in the study received a small token of appreciation (3 bars of soap, a monetary equivalent of 500 MWK [US $0.66]) after completing each survey. Parents or guardians of children who participated in the anthropometric measurement portion of the study received a small bag of puffed rice cereal (a monetary equivalent of 100 MWK [US $0.13]) after completing each survey. To avoid coercion into participation, participants were not informed of these tokens until after the survey had been administered.

All women who participated in the phone follow-up survey received mobile phone credit in the amount of 500 MWK (US $0.66) by means of a mobile airtime transfer. To avoid coercion into participation, women were not informed of this airtime transfer until after the survey had been administered.

### Primary Outcomes

At the designated 1-year and 2-year follow-up periods, the entire study sample of women was resurveyed to create a panel of individual women in which each woman and household would be observed over 3 time periods. In each follow-up round, we collected survey data on a range of primary outcomes of interest, which include (1) contraceptive use, including changes in contraceptive prevalence, changes in method mix, and adherence to methods (compliance and discontinuation) and (2) fertility and birth spacing outcomes, including pregnancy status, parity, and time since the last birth.

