### Analysis Plan

Analysis of quantitative study data will be conducted using STATA and R (the R Project), where appropriate. A descriptive analysis will be performed for all variables, and unadjusted comparisons between experimental arms will be conducted. Descriptive statistics will be performed, including frequencies, means, and standard deviations. In addition, chi-square tests and one-tailed *t* tests will be used to examine associations in the data. A *P* value <.05 will be considered statistically significant for all statistical tests that are conducted. Given our hypotheses of the impact of our intervention on our key outcomes, one-sided hypotheses tests will be conducted for all our main analyses. Continuous variables will be tested for normality and nonnormal values will be categorized or transformed appropriately.

Our main econometric specifications will estimate the intent-to-treat (ITT) effect of our family planning intervention on fertility and other outcomes by directly regressing our outcomes of interest on a binary variable indicating receipt of the intervention. The main econometric specification for estimating the ITT effect of our family planning intervention is defined as follows:

where *Y_it_* is the outcome variable of interest for woman *i* in the period *t*=0,1,2 for baseline, 1-year follow-up, and 2-year follow-up, respectively; *T_it_* is an indicator of assignment to the treatment arm; *X_it_* is a vector of individual-level covariates that are controlled for in the analysis; *_i_* is the individual-specific fixed effect; *Y_i0_* is the baseline level of the outcome; and *ε_it_* is the error term. Here, the outcome variables of interest include immediate, intermediate, and long-term outcomes mentioned in the previous sections.

We will conduct several subgroup analyses to examine how the family planning intervention effects vary across particular subpopulations. Subgroups of interest include pregnant women, new mothers, women who have previously used family planning, women who expressed a desire to space or limit births at baseline, poorer women, and women with low educational attainment. In addition, we will estimate heterogeneous treatment effects for girls, older children, and high-parity households.

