### Sample Size and Power Calculations

The sample size of this study was powered to primarily identify the effect of using family planning on fertility; however, we will also examine the effects of the intervention on other maternal and child health outcomes of interest, in addition to key social and economic measures of well-being. On the basis of the preliminary power calculations for our primary outcomes of interest, a total of 2000 women were needed to be enrolled in the study. Of the women who were enrolled, the family planning intervention, baseline survey, and 2 follow-up surveys were administered to 1000 women (the treatment group), whereas a basic family planning information package, the baseline survey, and 2 follow-up surveys were administered to the other 1000 women (the control group).

Our target baseline sample consists of 2000 women who met the eligibility criteria and who consented to participate in the study. Previous research studies in Accra, Ghana, have found that 32% of initially screened women either did not meet the eligibility criteria or refused to participate [20-22]. Therefore, to meet our target sample size of 2000, we would need to screen 3000 households if we conservatively assumed a combined ineligibility or refusal rate of 32% from the screening. Of the 2000 women who were to be recruited into the study at baseline following the initial screening process, 1000 women were to be randomly assigned to the intervention arm and the remaining 1000 women were to be randomly assigned to the control arm. On the basis of prior study findings from Zambia [13], we expected an attrition rate of 27% in the sample over a 2-year study period, which would leave us with an attrition-adjusted sample size of 730 women in each treatment arm, or 1460 women overall, at the end of the 2-year study period.

Given this attrition-adjusted sample size, we have powered our study to detect effects in 2 key outcomes, namely changes in contraceptive prevalence and fertility, the latter measured by the number of births per woman.

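### The primary births outcome is not limited to births conceived after randomization, so index births of women pregnant at entry add avoidable noise to baseline-adjusted or change-in-parity analyses

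*Protocol article*

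**What the plan says.** - **Outcome.** Protocol article, Primary Outcomes: "fertility and birth spacing outcomes, including pregnancy status, parity, and time since the last birth". Sample Size and Power Calculations names fertility as one of two powered outcomes, "the latter measured by the number of births per woman".
- **Entry.** Study Sample and Inclusion Criteria admits women who "were either currently pregnant or had given birth within 6 months from the time of the baseline screening".
- **Timing.** "Two follow-up surveys were conducted 1 and 2 years after the baseline survey".
- **Model.** The Analysis Plan lists an assignment indicator, individual-level covariates that are not itemised, an individual fixed effect, and a term that "is the baseline level of the outcome". The equation itself is not legible in the text available, so its exact form cannot be read.
- **Balancing.** The eight factors under Randomization include "number of living children, months since last live birth, current use of family planning". Current pregnancy is not named.
- **Testing.** A P value "<.05 will be considered statistically significant for all statistical tests", and "one-sided hypotheses tests will be conducted for all our main analyses".

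No section separates the birth from the pregnancy present at entry (the index birth) from later births.

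**The concern.** Take two women with the same obstetric history, one interviewed two months before her delivery and the other two months after. The first has a baseline parity one lower, and gains one birth during follow-up that was conceived before assignment. The second gains nothing from that birth. Their difference in parity gain reflects interview date, not treatment. Baseline parity cannot tell them apart, because it mixes entry status with every earlier birth. A woman fixed effect cannot either, because the index birth is a change over time within the woman.

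Only pregnancies conceived after randomization can respond to the intervention. If index births stay in the count, the analysis carries a large component of variance unrelated to treatment. A null result on parity could then be read as no effect on repeat births when the analysis simply lacked precision. This matters because fertility is the outcome for which the trial says it was primarily powered.

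**Working it through.** **1. The plan's own figure.** Table 4 uses SD 2, 730 per arm and alpha .05. SE = 2 × √(2/730) = 0.1047; one-sided power = Φ(difference/SE − 1.645).

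| Difference (births) | Table 4 | Recomputed |
|---|---|---|
| 1.0 | 1 | 1.000 |
| 0.5 | 0.99 | 0.999 |
| 0.3 | 0.89 | 0.889 |
| 0.2 | 0.61 | 0.605 |

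The table reproduces one-sided. It concerns the level of parity, not the change.

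**2. Effect on the level of parity.** An index birth present with probability p adds variance of at most 0.25 (p = 0.5). If this is added on top of SD 2, SE = √(2 × 4.25/730) = 0.1079, about 3% larger. Power at 0.3 births falls from 0.889 to Φ(0.3/0.1079 − 1.645) = 0.872. On the raw level, earlier births dominate and the index birth hardly matters.

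**3. Effect on the change in parity.** The baseline outcome or the fixed effect takes out most of the spread from earlier births, so what remains is mainly births in the window. Assumptions not in the article: share pregnant p = 30-60%; gestation uniform over 1-8 months, or time since delivery uniform over 0-6 months; 95% of index pregnancies end in live birth; conception rate h = 10% or 20% a year from 6 months postpartum; births counted to month 24. From the article: 1669 women at Year 2, so 834.5 per arm. Simulated results:

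| p | h | New births per woman | Index share of births in window | Variance, all births | Variance, new births only | Ratio of variances | Ratio of SEs |
|---|---|---|---|---|---|---|---|
| 0.3 | 0.10 | 0.077 | 79% | 0.252 | 0.071 | 3.5 | 1.9 |
| 0.3 | 0.20 | 0.148 | 66% | 0.286 | 0.126 | 2.3 | 1.5 |
| 0.5 | 0.10 | 0.065 | 88% | 0.283 | 0.061 | 4.6 | 2.1 |
| 0.5 | 0.20 | 0.126 | 79% | 0.308 | 0.110 | 2.8 | 1.7 |
| 0.6 | 0.10 | 0.060 | 90% | 0.275 | 0.056 | 4.9 | 2.2 |
| 0.6 | 0.20 | 0.116 | 83% | 0.297 | 0.102 | 2.9 | 1.7 |

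**4. Power at p = 0.5 for a 30% cut in new births.** The difference is 0.3 × 0.065 = 0.0196 (h = 0.10) or 0.3 × 0.126 = 0.0378 (h = 0.20). SE = √(2 × variance/834.5).

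| Analysis | SE, h = 0.10 | Power | SE, h = 0.20 | Power |
|---|---|---|---|---|
| Change in parity, all births | 0.0260 | Φ(0.754 − 1.645) = 19% | 0.0272 | Φ(1.390 − 1.645) = 40% |
| Same, adjusted for pregnancy at entry | 0.0142 | Φ(1.380 − 1.645) = 40% | 0.0177 | Φ(2.136 − 1.645) = 69% |
| Births from new conceptions only | 0.0121 | Φ(1.620 − 1.645) = 49% | 0.0162 | Φ(2.333 − 1.645) = 75% |

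**5. Bias, and whether baseline parity helps.** A separate simulation used 2000 trials, 730 per arm, half pregnant at entry, new births 0.20 against 0.15 (true difference −0.050), and new births unrelated to entry status.

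| Analysis | Mean estimate | SE | Power |
|---|---|---|---|
| Parity adjusted for baseline parity | −0.051 | 0.0313 | 0.50 |
| Change in parity | −0.051 | 0.0328 | 0.47 |
| Change, adjusted for pregnancy at entry | −0.050 | 0.0199 | 0.815 |
| New births only | −0.050 | 0.0198 | 0.815 |

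No analysis is biased. Adjusting for baseline parity leaves almost all the noise; adjusting for pregnancy at entry removes it. In step 4 the covariate recovers most rather than all of the power, because women pregnant at entry have less time for a further birth.

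**The case against.** The strongest reply is that a condensed article need not itemise covariates or counting windows. The covariate vector is open, a preanalysis plan is mentioned under Availability of Data and Materials, and pregnant women and new mothers are planned subgroups. Months since last live birth is a balancing factor and comes close to identifying entry status, since postpartum entrants are at 0-6 months and most pregnant entrants have a longer gap or no previous birth.

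Much of this stands. One cannot say that pregnancy at entry will be left out of the model, and entering months since last birth as a covariate would do much of the same work. But the outcome definition and the powered quantity are stated in the article, and neither excludes index births. Balancing at randomization gives no gain in the reported standard error unless the model adjusts for the factor, and subgroup results are not the main analysis.

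A reader might also infer three stronger things that the documents do not support:

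- **That pregnancy status at follow-up is contaminated by the index pregnancy.** The nominal gap of one year exceeds a gestation. Only a woman in early pregnancy at a late baseline, re-interviewed months ahead of her anniversary, could still carry it at Year 1. At Year 2 it is impossible.
- **That the effect is hidden by bias.** Index births fall alike on both arms, and step 5 shows no bias.
- **That chance imbalance in the share pregnant is a further harm.** It is ordinary sampling error, already inside the larger standard error.

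**Conclusion.** The point holds as a loss of precision in the births-per-woman outcome, not as a bias. Its size depends on the analysis. On the raw level of parity with SD 2, the index birth adds about 3% to the standard error. In a change analysis without adjustment for entry status, the standard error is about 1.5-2.2 times that for births from new conceptions; adjusting for baseline parity barely helps (0.0313 against 0.0328 in step 5). The article's model variables point towards this second kind of analysis.

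The ratios and powers rest on the assumed share pregnant, conception rate and 30% effect, none of which the article gives. The direction does not depend on them: index births of women pregnant at entry cannot respond to treatment, and baseline parity does not identify them.

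**What to change.** 1. Define the fertility outcome as births, and pregnancies, from conceptions after randomization, and exclude the pregnancy present at baseline from the counts at both follow-up waves.
2. Name baseline pregnancy status as a covariate in the fertility models. In a model with woman fixed effects a time-constant covariate drops out, so it must enter as an interaction with survey wave.

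The covariate alone recovers most of the lost precision; the redefinition recovers the rest and ties the outcome to the trial's stated interest in subsequent pregnancy. The cost is wording in the outcome definition and model. Table 2 shows pregnancy and fertility data collected at all three waves, and the article describes the primary analysis as still under way. The small downside is that a few conceptions close to baseline must be dated from reported gestation, with some error.
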